## Abstract

**Background:**

Attention-deficit/hyperactivity disorder (ADHD) affects 4% to 5% of the general population. Homework sessions are frequent conflictual moments characterized by increased anxiety in children and stress in their parents, contributing to a lower family quality of life. Children with ADHD experience more severe homework problems than typically developing peers. Poor academic performance in individuals with ADHD is partly attributed to challenging homework. Psychoeducational and school-based approaches are time-consuming and not fully accessible to professionals. Digital tools, such as smartphone and tablet apps, might offer an interesting alternative. We present our digital homework support program for children and adolescents, known as “Programme d’Aide Numérique aux Devoirs pour Enfant avec TDA-H” (PANDAH), along with the study protocol of our ongoing randomized controlled trial.

**Objective:**

This study aims to test PANDAH’s efficacy in improving homework performance and family quality of life.

**Methods:**

Individuals aged 9-16 years with an ADHD diagnosis and no comorbid psychiatric disorders are included. This is a multicenter study involving 9 reference centers for ADHD in France. The study comprises (1) a 3-month period with a randomized controlled trial design, where participants are divided into 2 parallel groups (group 1: care as usual or waiting list; group 2: PANDAH app), followed by (2) an extension period of 3 months (months 3-6), during which all participants will have access to the app. This second phase serves as a crucial incentive for patients initially randomly assigned to group 1. Assessments will be conducted at baseline, month 3, and month 6 for each patient by trained psychologists. The primary end point will be the global Homework Performance Questionnaire (HPQ), Parent version score at 6 months. The main analysis will adhere to the “intent-to-treat principle” (all patient data will be analyzed according to their initial group determined by randomization). We expect (1) HPQ score improvement in individuals using the app during the first 3-month period compared to individuals not using the app; (2) greater HPQ score improvement for individuals using the app for 6 months compared to those using the app for 3 months only; and (3) adherence to the PANDAH program, measured with in-app metrics.

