### Study Design

The primary investigator’s center is the Department of Child and Adolescent Psychiatry at Nantes University Hospital Centre, which includes a clinical research unit in psychiatry, addictology, and child and adolescent psychiatry. The study will consist of a 3-month period with a randomized controlled trial design, where participants are divided into 2 parallel groups (group 1: care as usual or waiting list; group 2: PANDAH app). This is followed by a 3-month extension period (month 3 [M3] to month 6 [M6]), during which all participants will have access to the app (Figure 1). This second phase serves as an incentive for patients initially randomized into group 1. Assessments will be conducted at baseline (M0), M3, and M6 for each patient. Baseline evaluations will be performed by trained psychologists at inclusion and will include age, sex, school grade, treatment history, Child Behavior Checklist, Hamilton Anxiety Scale, ADHD Rating Scale, and Homework Performance Questionnaire (HPQ) [32] with parents. Interviews will last approximately 2 hours and 30 minutes, including instructions for using the app for group 2. Evaluations at M3 and M6 will be similar (2 hours and 30 minutes), allowing the assessment of the maintenance of effects and efficacy.

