### Primary End Point

The primary end point will be the global score on the HPQ, Parent version (HPQ-P) [32]. This 12-item questionnaire, developed in partnership with parents using focus groups and interviews, uses a 4-point scale.

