### Secondary End Points

The secondary end points include (1) global and domain scores of HPQ-P at M6 [32]; (2) global and domain scores of HPQ, Teacher version at M3 and M6 [32]; (3) Patient Pediatric Quality of Life Inventory and Pediatric Quality of Life Inventory Family Impact Module at M3 and M6 [33,34]; (4) global score of Homework Problem Checklist for Parents at M3 and M6 [35,36]; (5) Inattention and Hyperactivity scores from Conners 3 at M3 and M6 ; (6) in-app scores for fill rate and number of complete app sessions during the M0-M3-M6 period; (7) Children’s Depression Rating Scale–Revised in Adolescents and Hamilton Anxiety Scale at M3 and M6; and (8) Likert scale for teachers at M3, M6, and end of the academic year (Mx) regarding changes in students’ academic levels: “Degraded/Slightly Degraded/Slightly Improved/Improved” [37].

Secondary criterion 6 will further allow us to assess the actual usage of the app by estimating the time the app is open and the time of interaction (using fingers) with the app. This way, we can evaluate whether the child is not solely focused on the app but engaged in other activities as well.

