### Statistical Analysis

The primary analysis will adhere to the “intent to treat principle,” analyzing all patient data based on their initial group determined by randomization.

Descriptive statistical analyses will be conducted for categorical data (number and percentage) and continuous data (range, mean, median, and IQR).

Confirmatory factor analysis will be applied preliminarily to the HPQ-P and HPQ, Teacher version questionnaires to assess construct validity. Adequate fit will be considered if the Comparative Fit Index≥0.90 and the root mean square error of approximation≤0.08. Meaningful differences between well-fitting models will be assessed using Δ Comparative Fit Index>+0.01. Reliability will also be assessed using Cronbach α, considered satisfactory if above 0.7.

Cross-sectional comparisons (eg, M3) of continuous and categorical data will use linear or logistic regression, adjusting for M0 if appropriate based on the data collection schedule.

Longitudinal data will be analyzed and compared between the 2 groups using linear mixed models with random effects to account for repeated measurements within patients. Different models, including random intercept or slope models, will be assessed based on the Akaike information criterion, and normality and homoscedasticity of residuals will be examined. A dummy variable reflecting the switch at M3 from the control group to the PANDAH app group will be included in the models (M0 to M6).

Assuming a mean difference of 0.4 on the global score of the HPQ-P at M3 between the 2 groups, with a common SD of 0.9, a total of 264 patients (n=132, 50% in each group) is required to detect this difference with a 5% type I error and 95% power in a 2-tailed *t* test. Assuming 0 attrition (no loss to follow-up) due to proximal assessments at M3, saturation of the child psychiatrist network, and no removal or relocation of families shortly after the school year begins, our aim is to include precisely 264 patients in the PANDAH trial.

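### The primary time point contradicts itself: the abstract fixes HPQ-P at 6 months, when both arms have the app, while the sample size rests on M3 and M6 is listed as secondary

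*Protocol article*

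**What the plan says.** Four places in the protocol article bear on when the primary end point is measured.

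- **Abstract, Methods:** "The primary end point will be the global Homework Performance Questionnaire (HPQ), Parent version score at 6 months". This is the only place that attaches a visit to the primary end point.
- **Primary End Point:** names the HPQ-P global score and describes the questionnaire, but gives no visit.
- **Secondary End Points:** item 1 is "global and domain scores of HPQ-P at M6". The global score at M6 therefore also ranks as secondary.
- **Statistical Analysis:** the sample size begins "Assuming a mean difference of 0.4 on the global score of the HPQ-P at M3 between the 2 groups", "with a common SD of 0.9", "with a 5% type I error and 95% power in a 2-tailed" t test. The assumption of zero attrition is also justified by how close the M3 assessment is.

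Study Design confines the randomised controlled comparison to the first 3 months. An extension from M3 to M6 follows, "during which all participants will have access to the app". The same section describes the later whole-cohort comparison as one between 3-month and 6-month users. Expected Findings lists app against no app over the first 3 months as the first hypothesis, and 6 against 3 months of use as the second.

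**The concern.** One variable at one visit cannot be both the primary and a secondary end point, and the section that should decide the matter is silent on the visit.

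The two candidate visits answer different questions. At M3 the arms differ in whether they have had the app, which is expected finding 1. At M6 both arms have had it and differ only in duration and starting date, which is expected finding 2. If the app works within 3 months and the delayed group then catches up, an intention-to-treat comparison at M6 correctly shows little or no difference, and the trial would be reported as negative on the end point its abstract names. The stated 95% power was not calculated for that comparison. Leaving two candidates open also means the 5% type I error would not be protected if the choice were made after the results were known.

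**Working it through.** **Inputs from Statistical Analysis:** difference 0.4 at M3, common SD 0.9, two-sided alpha 0.05, power 95%, 132 per group.

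**Step 1: reproduce the stated sample size.**

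n per group = 2 × SD² × (z₀.₉₇₅ + z₀.₉₅)² / difference² = 2 × 0.81 × (1.960 + 1.645)² / 0.16 = 131.6, rounded up to 132, so 264 in total. This matches the article. With the noncentral t distribution, 132 per group gives power of 94.9%. The arithmetic is right, and it powers the M3 comparison.

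**Step 2: apply the same sample size to M6.**

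The article gives no expected difference at M6, so the values below are assumptions, with the SD kept at 0.9. The standard error of the difference is 0.9 × √(2/132) = 0.1108. The noncentrality is the difference divided by 0.1108, on 262 degrees of freedom with critical value 1.969. The totals in the last column use the normal formula of step 1.

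| Assumed M6 difference | Reading | Noncentrality | Power with 132 per group | Total needed for 95% power |
|---|---|---|---|---|
| 0.4 | whole gap persists | 3.61 | 94.9% | 264 |
| 0.3 | three quarters remain | 2.71 | 77% | 468 |
| 0.2 | half remains | 1.81 | 44% | 1054 |
| 0.133 | one third remains | 1.20 | 22% | about 2370 |
| 0 | full catch-up | 0 | 5% (alpha) | not attainable |

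**Step 3: what an open choice would do to the error rate.**

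Suppose success could be claimed at either M3 or M6, each tested at two-sided 5%. For two normal test statistics with correlation r, the chance of at least one false positive is 1 − P(|Z₁| < 1.96 and |Z₂| < 1.96). This gives 9.5% for r = 0.3, 9.1% for r = 0.5 and 8.3% for r = 0.7. The correlations are assumptions; the article gives none.

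**Step 4: which visit does the rest of the text support?**

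- *For M3:* the sample size, the attrition rationale, the listing of M6 as secondary, the 3-month randomised period and expected finding 1.
- *For M6:* the abstract sentence, the Introduction's reference to impact over a 6-month period, and expected finding 2.

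**The case against.** The strongest reply is that the Methods nearly all point to M3, so the abstract sentence is an isolated slip and no one plans to claim success at either visit. On that view the inflated error rate is hypothetical. This stands in part: no passage plans an either-or test, so the 8.3% to 9.5% applies only if the choice is left open. But the sentence is the only one that gives the primary end point a visit, and the section meant to define it does not correct it.

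A second reply is that M6 is a legitimate target. The Introduction speaks of a 6-month period, and the 6-against-3-month contrast is a declared hypothesis. That is fair: app against no app is the first expected finding, not the only stated aim. Yet if M6 were intended, its place among the secondary end points and the M3 sample size would both be wrong.

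A third reply is that the planned mixed models over M0 to M6 include a dummy variable for the control group's switch at M3, so the M6 data would not be reduced to a bare two-sample test. The power figures above do describe that bare comparison. However, the article does not make the mixed model the primary analysis or say which of its coefficients would be the primary contrast, so the model does not settle the question.

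Finally, the M6 differences are assumed. The gap of 0.4 could persist, for instance if both groups gain equally after M3, and power would then be as stated. The table includes that case.

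**Conclusion.** The contradiction is real and lies in the current text. The abstract ranks global HPQ-P at M6 as primary, the Secondary End Points section ranks it as secondary, and the sample size supports M3. The calculation of 264 is correct for M3, with power of 94.9%. For the end point the abstract names, that power holds only if the whole 0.4 difference survives 3 months of app use in the control group. Under assumed differences of 0.3 down to zero it falls from 77% to 5%, with SD 0.9, 132 per group and no attrition. The effect on type I error, up to about 9.5%, is conditional on the choice of visit staying open.

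Because this concerns the single result on which the trial will be judged, and recruitment has been under way since January 2024, it must be fixed before any comparative outcome data are examined.

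**What to change.** State in the abstract and in the Primary End Point section that the single primary end point is the global HPQ-P score at M3, compared between arms as randomised. Keep HPQ-P at M6 as secondary, and label it as 6 against 3 months of app use (early against delayed start). Add that the absence of a difference at M6 is not evidence against the app. Check the approved protocol and the registry record, neither of which was seen here, and bring them into line if they differ.

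If those documents show that M6 was intended, the secondary list and the sample size must be rewritten instead, with a justified M6 difference and attrition assumption for a comparison of 6 with 3 months of use.

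With M3 as primary, the cost is a wording amendment and, where needed, a registry update. No new data or patients are required, and 264 remains the sample size supported by the stated inputs. The price is that M6 ceases to be the headline result. If the approved protocol does name M6, the change is a formal change of primary end point and should be documented and dated as such.

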**Results:**

Recruitment began in January 2024, and the trial is ongoing.

**Conclusions:**

This study contributes to the digital transformation of health care. The use of smartphone apps in self-care and self-management is a societal phenomenon, and its implementation in the field of psychiatry is of particular interest. The app might serve as both valuable support for patients and an opportunity for parents to distance themselves from conflict-laden homework sessions. Since the market for smartphone apps in the health care and well-being sector is primarily industry driven, it is crucial to have an academic conception and evaluation of such digital tools.

**Trial Registration:**

ClinicalTrials.gov NCT04857788; https://clinicaltrials.gov/ct2/show/NCT04857788

**International Registered Report Identifier (IRRID):**

PRR1-10.2196/44553

## Introduction

Attention-deficit/hyperactivity disorder (ADHD) affects 4% to 5% of the general population [1,2]. Elementary school children with ADHD face severe academic challenges characterized by reduced seatwork completion, seatwork accuracy, on-task behavior, and homework performance compared to their peers [3,4]. Homework sessions are often tense moments marked by increased anxiety in children and stress in their parents, undeniably contributing to decreased family quality of life. Children with ADHD experience more severe homework difficulties than typically developing peers [5,6]. Longitudinal studies also indicate that homework performance during elementary school serves as a key predictor of later academic success for individuals with ADHD [7].

These issues persist into later school years, with middle and high school students with ADHD exhibiting poorer organizational skills, lower grades, increased truancy, and higher rates of suspension and grade retention compared to their peers [8-11]. Moreover, significantly fewer individuals with ADHD graduate from high school (68% vs 100% of controls) [11] or enroll in 4-year colleges and universities compared to controls (29.5% vs 76.8% of controls) [12]. In summary, academic underachievement is strongly associated with ADHD [13-19], and homework sessions could be a critical area of intervention to prevent this outcome.

To address this issue, several health care interventions are available, such as classroom management and behavioral consultations in school settings [20-22]. Although classroom management procedures and interventions have demonstrated short-term improvements in classroom behavior and seatwork completion and accuracy among children with ADHD in classroom and analog classroom settings [23-25], it is potentially beneficial to explore additional interventions targeting the academic functioning of children with ADHD, both at home and the parenting level. Research indicates a positive relationship between homework and achievement, with a stronger link observed in middle and high school [26].

Among the various behavioral parent training (BPT) programs for children with ADHD, two programs have focused on homework functioning: (1) the Family School Success Program [27] and (2) Parents and Teachers Helping Kids Organize [28]. Both programs incorporate effective components of BPT, such as consistent responses, time-out, goal setting, rewards, and positive attention. They have demonstrated efficacy in improving parent-reported problematic behaviors during homework time, with moderate to large effect sizes ranging from 0.52 to 1.51 [28,29]. Furthermore, these academically focused BPTs have improved self-reported parenting strategies, teacher-reported homework problems, and parent- and teacher-reported organizational skills. Interestingly, children on stimulant medication who received BPT showed greater improvement in parent-reported homework management than their unmedicated peers [29]. However, none of these programs have incorporated new technologies thus far.

Over the past 4 years, we have been developing a smartphone app to assist in homework management within therapeutic groups, aiming to help both parents and patients improve their homework sessions and concentration. However, the real and perceived use of an app significantly impacts its usefulness [30]. Therefore, to be efficient and reduce attrition, a digital tool needs a specific design; an intuitive user interface; and the addition of an artificial intelligence module to create an algorithm that can analyze, predict, and provide suitable personalized advice. As a result, we developed *Programme d’Aide Numérique aux Devoirs pour Enfant avec TDA-H* (PANDAH; “a digital program to help children with ADHD during homework sessions” in French) to support children with ADHD during their homework sessions with minimal or no parental assistance.

This study aims to investigate the impact of PANDAH on children and adolescents aged 9 to 16 years with ADHD over a 6-month period, focusing on homework performance and well-being.

## Methods

### Recruitment

This multicenter study involves 9 reference centers for ADHD in France, which are specialized centers covering specific geographic areas with multidisciplinary teams experienced in ADHD diagnosis and treatment. We plan to include a total of 360 patients with ADHD from waiting lists of reference centers (median waiting time in France is 9 months) [31]. The inclusion and exclusion criteria are shown in Textbox 1.

Inclusion and exclusion criteria.

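### The article gives two enrolment targets, 360 and 264; only 264 follows from the stated inputs, so the number at which recruitment stops is not fixed

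*Protocol article*

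**What the plan says.** The protocol article gives the size of the trial twice.

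- **Methods, Recruitment:** "We plan to include a total of 360 patients with ADHD from waiting lists of reference centers". No derivation or allowance is attached.
- **Methods, Statistical Analysis, last paragraph:** the calculation begins "Assuming a mean difference of 0.4 on the global score of the HPQ-P at M3 between the 2 groups", "with a common SD of 0.9", and concludes that "a total of 264 patients (n=132, 50% in each group) is required to detect this difference" "with a 5% type I error and 95% power", using a two-tailed t test. It then sets expected loss at nil ("Assuming 0 attrition (no loss to follow-up) due to proximal assessments at M3") and closes with "our aim is to include precisely 264 patients in the PANDAH trial".

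The Results section reports that recruitment opened in January 2024 and is under way.

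**The concern.** The total sample size is a core design figure, and here it takes two values that cannot both be right. Each sentence describes how many patients the trial will include, and the second does so with a word that excludes reading 264 as a minimum.

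Enrolment is in progress at nine centres, so the target is a working instruction as well as a planning figure. A centre or reader following Recruitment would continue to 360. One following Statistical Analysis would stop at 264. If 264 is enough, a further 96 families would go through assessments of about two and a half hours at each time point for no stated reason. If 360 is intended, the published justification does not support the trial being run.

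**Working it through.** **Inputs, all from Statistical Analysis unless noted**

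| Input | Value |
|---|---|
| Difference in HPQ-P global score at M3 | 0.4 |
| Common SD | 0.9 |
| Type I error | 5%, two-sided |
| Power | 95% |
| Allocation | 1:1 |
| Attrition | 0 |
| Target in Statistical Analysis | 264 |
| Target in Recruitment | 360 |

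**1. Reproduce 264.** By the normal approximation:

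n per group = 2 × (1.960 + 1.645)² × (0.9/0.4)² = 131.6, rounded up to 132, which gives 264 in total.

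The article's figure is correct for its inputs. An exact noncentral-t calculation asks for 133 per group (266), a negligible difference. At 132 per group the exact power is 94.9%; the normal approximation gives 95.1%.

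**2. Try to reach 360 (180 per group) from the same inputs.**

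- *Another power level.* Two-sided, 80%, 90%, 95% and 99% power need 80, 107, 132 and 187 per group. One-sided, they need 63, 87, 110 and 160. None is 180.
- *An attrition allowance.* Dividing 264 by one minus the loss gives 294 at 10%, 330 at 20% and 352 at 25%. Reaching 360 requires a loss of 1 − 264/360 = 26.7%. The article assumes zero, so this route is closed by its own text.
- *A number screened.* Recruitment speaks of patients included. Study Design describes screening as a separate step in which diagnosis and eligibility are confirmed before consent. The sentence therefore does not read as a screening count.

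**3. Size of the gap.** 360 − 264 = 96 patients, and 96/264 = 36%.

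**4. What each target delivers, on the article's assumptions and with no loss.**

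| | 264 (132 per group) | 360 (180 per group) |
|---|---|---|
| Power for 0.4, noncentral t | 94.9% | 98.8% |
| Difference detectable with 95% power, normal approximation | 0.40 | 0.34 |

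The second row is 0.9 × (1.960 + 1.645) × √(2/n), with n = 132 or 180.

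**5. Sensitivity to loss.** The article gives no attrition figure other than zero, so a range of 10% to 25% is assumed here only to show scale. Over that range, power falls from about 93% to 88% if 264 are enrolled, and from about 98% to 95% if 360 are enrolled.

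**The case against.** The strongest reply is that the two numbers do not have equal standing. Only 264 is derived, it reproduces, and it is stated emphatically in the paragraph whose purpose is to justify the sample size. A reader may fairly treat 264 as the justified target and 360 as a leftover or a capacity figure. It does equal 40 for each of the nine centres, although the article says nothing of the kind. It can be added that neither number leaves the trial short of power on its own inputs, and that the conflict does not in itself bias the randomised comparison.

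All of this stands, and it limits the consequence. It does not remove the contradiction, because Recruitment still announces a different total and the article does not say which one governs. Nor is this a matter of condensing a longer protocol: two incompatible values are printed, and nothing has been left out.

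Four stronger readings are tempting, and the article does not support them.

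- *That power is undefined.* It is ambiguous between two adequate values. These are also planning values for an unadjusted t test. The article allows baseline adjustment and mixed models, so they are not the power of the final analysis.
- *That enrolment will be stopped on the strength of the results.* No interim analysis or outcome-dependent rule is described. Two published targets leave room for such a choice, but nothing shows that one is intended.
- *That 360 is 264 inflated for a 26.7% loss.* That percentage is simply back-calculated from the two totals and appears nowhere in the article.
- *That the full protocol or the registry entry is also wrong.* Neither is shown, and either may carry one consistent figure.

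**Conclusion.** The point holds as an internal inconsistency; no calculation in the article is wrong. The total sample size is misstated in one of two places, by 96 patients (36% of 264). The stated inputs support 264. They do not support 360, which has no basis in the article and cannot be an allowance for loss when the loss is set at zero.

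The consequence is that the number at which recruitment stops is not fixed. Planned power is about 95% or about 98.8% depending on which target governs, so the trial is not underpowered either way. Those figures rest on the article's difference of 0.4, SD of 0.9, two-sided 5% level, equal groups and no attrition. The choice would matter more if the no-loss assumption failed, since only 360 leaves a margin, but the article gives no basis for saying how large any loss would be.

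Because recruitment is under way, the figure should be settled promptly, preferably before enrolment reaches the smaller number.

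**What to change.** Give one enrolment target, identically, in Recruitment and in Statistical Analysis.

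- If the target is 264, change the figure in Recruitment. The existing derivation then stands as written.
- If the target is 360, state its actual basis. If that basis is an expected loss, put the real allowance in place of the zero-attrition assumption and give the evaluable number it is meant to secure. If it is something else, say what, and restate the power for 360. A loss rate worked backwards from the two totals should not be supplied as the rationale.

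In either case, add a sentence that enrolment stops at the stated number without reference to outcome data.

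The cost is a short correction to the article, once the sponsor confirms which number is operative. No change to the design or the analysis is needed. Whether any other trial document needs the same correction cannot be judged from what is shown.
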